## Introduction

Chronic obstructive pulmonary disease (COPD), characterized by airflow limitation and persistent respiratory symptoms caused by a combination of small airway disease (obstructive bronchitis) and lung parenchymal destruction (emphysema), is the third most common cause of death [1, 2]. In 2019, 212.3 million prevalent cases of COPD were reported globally, including 3.3 million deaths and 74.4 million disability-adjusted life years [3, 4]. Continued exposure to COPD risk factors and an aging population have made COPD a global public health challenge [5]_._ Clinical treatment of stable COPD aims to reduce symptoms, decrease the frequency and severity of acute exacerbations, improve health status, and enhance exercise tolerance. Despite the importance of bronchodilators, glucocorticoids, mucolytics, and antibiotics as clinically indicated drugs in treating stable COPD, there are inevitable side effects [6]. For example, beta_2_-agonists may cause hypokalemia and tardive dyskinesia [7, 8], antimuscarinic drugs cause dry mouth [9], glucocorticoids increase the incidence of pneumonia [10], and antibiotics cause bacterial resistance and tinnitus [11]. Moreover, some patients still have symptoms that cannot be effectively controlled based on conventional medications. Therefore, it is imperative to explore new treatment options that are safe and effective, with fewer side effects, to improve patient symptoms further, reduce acute exacerbations, and minimize the side effects of conventional drug therapy.

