### Participants

#### Inclusion criteria

Participants who meet the diagnostic criteria for COPD according to the Global Initiative for COPD and conform to all the following criteria will be included in the study [28]: 1) stable condition without acute exacerbation in the last 4 weeks; 2) age between 40 and 80 years, both sexes; 3) FEV1pre between 25 and 80% after inhaled bronchodilators; 4) at least 1 moderate or severe acute exacerbation within the past year; 5) receiving stable Western medication within the previous 3 months; 6) willing to cooperate with the study and sign an informed consent form.

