### Statistical analysis

Analyses will be performed according to the intention-to-treat (ITT) principle and will be statistically analyzed for all randomized participants. Missing data will be filled in using the multiple imputation method. Statistical analysis will be performed by the Chinese Cochrane Center, West China Hospital, Sichuan University, China and SAS software will be used for statistical analysis. Quantitative indicators are described using mean, standard deviation, median, 25th percentile and 75th percentile. Categorical indicators are described using frequencies and percentages. The normality of the data will be verified by the Kolmogorov–Smirnov test (K-S test). Equality of variance between observed variables will be verified by Levene's Test. Baseline data will be analyzed using chi-square or Fisher's exact test for categorical indicators and ANOVA or the Kruskal–Wallis H test for quantitative indicators.

The primary outcome will be analyzed by generalized linear mixed effects model. Fixed effects included group, age, COPD sub-type, and years of smoking; random effects included sub-center, time, and time × group interaction. Secondary outcomes will be analyzed using linear mixed effects models, with fixed and mixed effects containing the same variables as the primary outcome indicators.

We will include participants who completed no less than 80% of their treatments in the per-protocol set (PPS). Several sensitivity analyses will be conducted to examine the robustness of the finding. First, we will exclude the participants with acute exacerbations during treatment period. Second, we will exclude the participants who have infected COVID-19 during treatment period. We will analyze each of the subgroups that may potentially influence the outcomes, including: 1) Age: < 60 or > 60; 2) Smoking history: yes or no; 3) FEV1%pre: ≤ 50 or > 50; 4) Type of COPD: chronic bronchitis type or emphysema type. Statistical test will be a 2-sided test, with *P* < 0.05 considered statistically significant.

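### The two sensitivity analyses drop participants for events after randomisation, so they do not test the robustness of the ITT result; separately, the age subgroup leaves out participants aged exactly 60

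*Protocol article*

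**What the plan says.** All points are in the protocol article, under Statistical analysis unless stated.

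- Main analysis: "Analyses will be performed according to the intention-to-treat (ITT) principle and will be statistically analyzed for all randomized participants". For incomplete data: "Missing data will be filled in using the multiple imputation method". A per-protocol set is added.
- Purpose of the further checks: "Several sensitivity analyses will be conducted to examine the robustness of the finding".
- The two checks named: "First, we will exclude the participants with acute exacerbations during treatment period" and "Second, we will exclude the participants who have infected COVID-19 during treatment period".
- Exacerbation is not incidental to this trial. The Introduction gives as part of the case for new treatments that they should "reduce acute exacerbations, and minimize the side effects of conventional drug therapy". Under Secondary outcomes, moderate and severe exacerbations in follow-up are the eighth outcome, and the outcome descriptions also schedule counts at weeks 0, 4, 8 and 12.
- Treatment compliance has participants resume their remaining sessions after an exacerbation or a COVID-19 quarantine.
- Subgroups are listed separately, after the sensitivity analyses. The first is "1) Age: < 60 or > 60". The eligible range under Inclusion criteria is "age between 40 and 80 years, both sexes".

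**The concern.** A sensitivity analysis of an ITT result should keep the question and the randomised comparison and vary an assumption, such as the one behind the imputation. These two analyses change the population instead, by events that occur after allocation.

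For exacerbation the choice is awkward. Every participant has had at least one moderate or severe event in the past year, so events within 12 weeks are likely. The SGRQ includes symptom frequency and severity, so an exacerbation plausibly worsens the score. If acupuncture also prevents some exacerbations, the control arm loses more of its poor-prognosis participants than the acupuncture arms do, and those who remain are no longer comparable. The exclusion could then make a sound result look fragile, and agreement with ITT would say little about whether the imputation assumptions were reasonable.

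The COVID-19 exclusion has the same form. Scheduled sessions range from 0 (waiting list) to 36, so exposure to infection, or its detection, could in principle differ between arms.

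The age cut is a different and smaller matter: a 60-year-old is eligible but belongs to neither level, so the two levels need not add up to the analysis set.

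**Working it through.** **The plan's own figure.** The article gives no figure for these analyses. Its sample size uses mean SGRQ changes of −7.1 (three times a week), −2 (sham) and −0.8 (blank control), SD 14.2, two-sided 0.05 and 80% power. A three-group one-way ANOVA F test with these inputs gives 88 per group, as stated; 88 / 0.8 = 110 and 5 × 110 = 550. The point does not depend on this, but the planning means set the scale.

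**Scale.** Assuming normal changes and response at −4 or lower:

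- three times a week: Φ((−4 + 7.1)/14.2) = 58.6%
- sham: Φ((−4 + 2)/14.2) = 44.4%
- difference: 14.2 percentage points.

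**Effect of excluding exacerbators when SGRQ is truly unaffected.** Assumed model, since the article gives no event rates:

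- Each participant has a standard normal tendency U and exacerbates if U < z_p, where p is the event risk in the arm and z_p = Φ⁻¹(p).
- SGRQ change = −2 − r × 14.2 × U + noise, total SD 14.2, the same in both arms.
- Control risk is 20% to 40%, risk ratio (RR) 0.5 to 0.7, correlation r 0.3 to 0.5.

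The responder proportion among those retained is

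(1/(1 − p)) ∫ from z_p to ∞ of φ(u) Φ((−4 + 2 + 14.2 r u)/(14.2 √(1 − r²))) du.

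| Control risk | RR | r | Control responders | Acupuncture responders | False difference (points) | Retained, control / acupuncture |
|---|---|---|---|---|---|---|
| 20% | 0.7 | 0.3 | 48.5% | 47.4% | −1.1 | 80% / 86% |
| 20% | 0.5 | 0.5 | 51.1% | 47.9% | −3.2 | 80% / 90% |
| 40% | 0.7 | 0.3 | 52.1% | 49.9% | −2.2 | 60% / 72% |
| 40% | 0.5 | 0.5 | 57.5% | 51.1% | −6.4 | 60% / 80% |
| any | 1.0 | any | equal | equal | 0 | equal |

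With all randomised participants kept, both arms are at 44.4% and the difference is 0.

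**Same model with the planned effect.** Replacing −2 by −7.1 in the acupuncture arm, the 14.2-point difference becomes 13.3 points in the mildest case (20%, 0.7, 0.3) and 8.4 points in the strongest (40%, 0.5, 0.5).

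**Second model.** A logistic model with a shared frailty and no true effect gives −0.6 to −1.7 points at risks of 25% vs 15%, −0.8 to −2.6 points at 35% vs 20%, and 0 at 25% vs 25%.

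**How extreme is 40%?** Under a constant rate, 40% in 12 weeks implies −ln(0.6) × 52/12 = 2.2 events a year. One event a year gives 1 − exp(−12/52) = 21%. The top of the range therefore needs a high event rate together with a strong treatment effect and a strong correlation.

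**Age.** There are 41 whole-year ages from 40 to 80. If ages were uniform, 550/41 = 13 participants (2.4%) would be in neither level. With ages assumed normal, mean 62 and SD 8, it would be about 27 (4.9%).

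**The case against.** The strongest reply is that the primary inference is untouched: ITT on all randomised participants stays the main analysis, and the exclusions are pre-stated and secondary. That stands, and it limits the severity.

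It is also fair that the bias needs acupuncture to change exacerbation risk. The earlier acupuncture studies summarised in the Introduction concern dyspnoea, walking distance, lung function and quality of life, not exacerbations. The exacerbation outcome is defined for follow-up, although counts are also taken during treatment. The risk ratios above are assumptions, and most of the range is small beside 14 points.

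Several stronger readings are tempting but not supported:

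- *The checks are biased by design and can neither support nor contradict the result.* With equal event risk the bias in this model is zero. Where it does run against acupuncture, a positive ITT result that survives the exclusion is, if anything, conservative support.
- *Excluding exacerbators removes the treatment failures and so flatters acupuncture.* Exacerbation is not the definition of non-response, and in the scenarios above the false difference goes the other way.
- *The COVID-19 exclusion is biased in the same way.* The article gives no mechanism and no sign that infection differs by arm. The three-times-a-week and sham arms both have 36 sessions, so the attendance argument does not reach that comparison; it could apply only where attendance differs, as against the waiting list or between frequencies.
- *The age gap weakens the robustness checks.* Age is a baseline variable in a subgroup analysis. The gap causes no post-randomisation selection.

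What remains is that the article itself assigns these exclusions the task of testing robustness, and they are not suited to it. That is a stated choice, not a detail left to an unseen analysis plan. The age cut is probably not a text-extraction fault, since the FEV1 cut in the same list kept its ≤ sign and is complete.

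**Conclusion.** The concern holds in a limited form. Both named sensitivity analyses drop randomised participants for events after randomisation, so they answer a different question from the ITT analysis and do not test its assumptions. The exacerbation exclusion matters most. If acupuncture lowers exacerbation risk and exacerbation goes with worse SGRQ, it produces a false responder difference of about 1 to 6 points against acupuncture under the assumed inputs, and none if event risk is equal. The upper end rests on the most extreme combination. Bias from the COVID-19 exclusion is possible but not shown. The primary ITT analysis is not affected, so this should be corrected but does not threaten the trial's main conclusion.

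The age boundary is a separate, minor slip affecting roughly 2% to 5% of participants under the assumed age distributions.

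**What to change.** 1. Base the robustness checks on all randomised participants: for example, vary the multiple-imputation assumptions, or set only the COVID-affected SGRQ values to missing and impute them within arm.
2. Keep the two exclusion analyses only as labelled supplementary analyses, with the number excluded reported by arm, so that a reader can see whether event risk differed.
3. Optionally add a supplementary composite analysis that counts a treatment-period exacerbation as non-response. State that it targets a different endpoint: a participant with an early exacerbation and a 4-point SGRQ improvement would count as a failure. It should not replace the checks in item 1.
4. Define the age subgroup as < 60 vs ≥ 60.

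The cost is a wording change in the protocol or analysis plan and a little programming. No additional data are needed beyond the exacerbation and COVID-19 information that the planned exclusions already require.

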### Treatment compliance

The number of expected and actual treatments for each patient will be counted to assess the patient's compliance. In patients whose treatment is discontinued due to an acute exacerbation, the patient will continue to complete the rest of the treatment after a week of stabilization. Patients who have been quarantined due to COVID-19 will continue to complete the rest of their treatment once they are unblocked. A patient will be regarded as compliant if receiving > 80% of the expected treatments.

### Quality control

The trial protocol was reviewed and revised by experts in acupuncture, respiratory medicine, methodology, and statistics. Standard operating procedures (SOPs) will be developed in advance, and training sessions will be held before the start of the study to provide standardized training for investigators at each center and to ensure that each researcher is familiar with the research process and the specific implementation details. The participants in the trial should be fixed, and the recording methods and judgment criteria should be unified to ensure that the scale assessment, data management, and completion of the CRF are carried out under uniform standards. The data inspector will conduct quality control checks at each research center every 3 months to ensure that all elements of the study protocol have been strictly adhered to, as well as the correctness of the completed information, and to generate quality control analysis reports.

### Data collection, management and monitoring

Data will be collected by telephone or on-site questioning by researchers not involved in the statistical analysis and treatment. The statistical company and the research team are jointly responsible for the data management of this project. The investigator fills out the clinical trial record requirements: timely, accurate, complete, standardized and truthful. The monitor verifies that the investigator follows the trial protocol during the experiment and regularly checks subjects' informed consent and inclusion at each sub-center. Data entry personnel will need to be trained to perform data entry. The CRF will be filled into the Electronic Data Capture (EDC) system by two independent data entry operators to ensure the accuracy of the data. Any changes to the data will be tracked in the EDC system.

## Discussion

As the third leading cause of death worldwide, COPD affects patients’ health and quality of life and imposes a substantial economic burden on society.

The GOLD guideline states that the primary goal of managing stable COPD is to relieve symptoms and reduce the risk of future acute exacerbations. The GOLD recognizes the SGRQ as the gold standard for evaluating COPD patients’ symptoms. SGRQ is a comprehensive disease-specific quality-of-life health questionnaire used in clinical trials with high validity, sensitivity, and reliability. The SGRQ is systematic, rigorous, detailed, and comprehensive and consists of three main sections: mobility, respiratory symptoms, and impact on daily life. The severity of COPD patients is closely related to their quality of life, and it has been found that the effectiveness of treatments and interventions for COPD patients can be reflected in their quality of life. The SGRQ is generalizable, and its scores have been validated repeatedly for different countries, races, ages, genders, and severities of respiratory diseases. The questionnaire covers the physical, emotional, and social aspects of the patient's life, correlates well with other clinical symptoms [42, 43], and is superior to other assessment scales [44, 45]. Pearson's analysis showed that the SGRQ, mMRC, and CAT had a good correlation (*P* < 0.05) and were consistent in the assessment of COPD, and all of them could be used to assess the degree of lung function impairment. The CAT scale is comprehensive, highly reliable, easy to understand, and time-consuming. The mMRC is also widely used in clinical practice because of its reproducibility, authenticity, and sensitivity. The 6-MWT is an objective sub-maximal exercise test. Because most of the daily activities of patients with COPD are at the sub-maximal level, the 6-MWD can reflect the functional compensatory capacity of patients to complete daily physical activities. The 6-MWD indicates the patient's functional compensatory capacity to perform daily physical activities. It can be used as an objective tool to assess the extrapulmonary effects of the disease on patients [38]. SF-36, as a universal measurement scale, can reflect the quality of life of patients with chronic diseases to a large extent. The pulmonary function test is a noninvasive tool for studying respiratory physiology, an objective indicator for determining airflow limitation with good reproducibility, and the gold standard for diagnosing COPD. It is vital for the diagnosis and differential diagnosis of COPD and evaluating severity, disease progression, prognosis, and response to treatment.

A clinically ideal placebo/sham acupuncture control should meet three basic principles: (1) placebo acupuncture has no or almost no specific therapeutic effect; (2) the needle is applied to a site that has no therapeutic effect; and (3) the subject cannot perceive the difference between placebo acupuncture and therapeutic acupuncture. However, due to the complexity of the acupuncture operation process, it is not easy to fully meet the above requirements. In most previous studies, non-acupoints or points on meridians not related to the treatment of disease were chosen as sham acupuncture points. One study found that acupoints have special efficacy in hand rheumatoid arthritis compared to non-acupoints. However, due to the nature of the disease and the size of the space of the acupoints, it is not possible to prove that the acupoints taken on the meridian side are non-acupoints [46]. Considering the above reasons, we will perform placebo acupuncture using flat-tipped needles at the same acupoints as the acupuncture group. In order to achieve a better blinding effect by convincing the patient, we will let the patient feel the pain of his/her stabbing but will not pierce the patient's skin. When inserted, the blunt tips of these special placebo needles produce a mild sting on the skin's surface but do not puncture the skin. Moreover, the needle retention on the base after needle insertion simulates regular needle insertion, which, combined with the retention and exit of the needle after needling, the subject can perceive it as an actual needling for optimal blinding. Considering that the natural course and regression of COPD disease are unpredictable, we additionally set up a blank control group that was not given any interventions except for regular medication.

This study has strict nadir criteria, and respiratory diseases that impact pulmonary function tests (for example, bronchial asthma, bronchiectasis, lung cancer, and lung resection surgery) will be excluded. Any additional use of Western medicine will be recorded in detail. Acupoint selection is a critical factor in acupuncture treatment. The acupoints selected for this study were based on data mining of modern acupuncture prescriptions for COPD. The most commonly used safe and effective acupoints were selected with consultation with clinical acupuncturists. The patient's prone position was also considered for easy manipulation [14, 47]. At the time of signing the informed consent form, subjects in the waiting-list group control group, the SA group, will be promised that compensatory treatment will be given at the end of the study. In this way, potential problems caused by patient disappointment will be overcome.

Inevitably, this study also has some limitations. First, due to the acupuncture operation's nature, it is impossible to blind the acupuncturist, which may also lead to bias. Second, the blunt-tipped needle touching the skin may have some stimulating effect on the acupoints, therefore it is necessary for us to set up a waiting-list control group.

## Conclusion

In conclusion, this study is a multicenter, randomized controlled trial to objectively evaluate the effectiveness and safety of acupuncture for stable COPD. It is the first RCT to investigate different acupuncture frequencies for stable COPD. It is proposed to explore the quantitative effect pattern of acupuncture from the perspective of acupuncture frequency influencing the acupuncture effect and to provide a reference for optimizing clinical decisions of acupuncture for chronic diseases.

### Trial status

The recruitment process began on April 17, 2022, and is anticipated to end on December 31, 2023.

## Data Availability

Not applicable; no data have yet been generated.

## Abbreviations

COPD: Chronic obstructive pulmonary disease
CAT: COPD assessment test
CRF: Case report form
EDC: Electronic data capture
LFSI: Lung function screening indicator
MCID: Minimal clinically important difference
mMRC: Modified-medical research council
PPS: Per-protocol set
PFT: Pulmonary function test
RA: Research assistant
MA: Manual acupuncture
SF-36: Medical outcomes study short form-36
SGRQ: St. George’s respiratory questionnaire
SA: Sham acupuncture
6-MWT: Six-minute walk test
6-MWD: Six-minute walk distance
